### Setting and recruitment

Recruitment shall take place at community-based child and family service institutions in the region of Hamburg, Germany, which will be chosen as recruiting centers if they reach a sufficient amount of families with their own qualified preventive service programs. As the SFP 10–14 is not routinely implemented in Hamburg, we will set up the required infrastructure for recruitment and program implementation in cooperation with and with support from the local authorities, as we have done for a similar study in the past [34]. Multiple recruitment strategies will be employed to reach a sufficient number of recruitment centers; recruitment includes distribution of written information and presentation of the program goals and study procedures by project representatives via local professional networks and specified agencies in the family health care and social service sector. Additionally, we will start initiatives to raise awareness in educational settings and at authority-level meetings.

Potential referrers will be informed about all aspects of the study and will agree to deliver both program versions in accordance with the study procedures, particularly those that concern randomization procedures, ethical standards, and qualified intervention delivery. Referring institutions will recruit potential participants and inform them about the prevention programs and the study procedures. Consent to participate in the family program (experimental or control) will take place prior to the baseline assessment. Interested families will be visited by a member of the research team for subsequent eligibility assessment and enrolment into the study. Written informed consent, with emphasis on withdrawal rights and ethical aspects as well as all relevant conditions of trial participation, will be obtained during the family visit. Baseline data will be collected before randomization. Trial participants are subsequently randomized to one of the two trial conditions. Recruitment/trial inclusion will be ongoing over a period of approximately 12 months. Figure 1 displays the anticipated CONSORT participant flow.

**Fig. 1 Fig1:**
[figure not shown]
Consolidated Standards for Reporting Trials (CONSORT) diagram: participant flow, detailing recruitment, training, intervention, and assessment schedule. ITT intention-to-treat, SFP-Mind Strengthening Families with Mindfulness, SFP 10–14 Strengthening Families Program for Parents and Youth 10–14

Program facilitators (experimental or control intervention) from cooperating institutions will take part in certified 3-day training (totaling approximately 24 h). Participating institutions shall receive a monetary compensation (€25 per intervention hour) from project funding. Participants in the trial will receive monetary compensation for their lost time for all assessments and at completion of the trial.

### Randomization procedure and blinding

Enrolled families will be randomized in a 1:1 allocation ratio into both intervention groups (SFP or SFP-Mind), as per a computer-generated randomization schedule stratified by recruitment center and intervention cycle. Multiple recruitment centers will be used for the trial. As soon as there are sufficient consenting participants for a single intervention cycle of seven sessions (typically six to eight families per intervention arm), the following random allocation process will be applied. First, an independent statistician will be informed by the study team about the sample size of participating families in the designed intervention cycle and create a concordant computer-generated randomization sequence, which will be concealed until assignment occurs. Second, a researcher independent to the study team will receive an anonymized index identification code for each family participating in that intervention cycle, including information on absolute time restrictions for participation (i.e., holidays, carers’ weekday absences), from the study team. The independent researcher will then randomly assign an index identification code to the randomized sequence. In the case that a defined time restriction of one family means incompatibility with the randomly allocated intervention timing, the family will be allocated to the other intervention arm by the independent researcher. This methodology is necessary to ensure family participation as some might have fixed time constraints to participate. In the event of reallocation due to individual time restrictions, the index identification code will be separately reported to the study team after the allocation process is finalized to allow for methodological scrutinization. See Additional file 2 for a flow chart of randomization procedures.

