### Analysis plan

Analyses are planned and supervised by the trial statistician (AD). Study eligibility and enrollment will be summarized according to the CONSORT statement [106]. Descriptive statistics of baseline variables will be assessed by intervention arm. Analyses will be based on the intention-to-treat population, thus including data from all participants who provide baseline data and are subsequently randomized to one of the two trial conditions. Missing follow-up data will be imputed using multiple imputation methods. For the primary analysis, a mixed, linear, repeated-measurement ANCOVA will be conducted, with alcohol initiation (in the form of an initiation index) as the dependent variable; group, time, and interaction between group and time and recruitment center as fixed effects; baseline scores of alcohol use as covariates; adolescent and intervention groups within the study arm as random effects; and time as a repeated effect. The contrast between both groups at the 18-month follow-up will be assessed in a confirmatory manner. We will report adjusted group differences with corresponding 95% confidence intervals (CIs), *p* values, and Cohen’s *d* effect sizes. A systematic examination of factors associated with loss to follow-up will be conducted. The two-sided type I error will be set at 5%. An additional analysis will be conducted on a per-protocol data set as sensitivity analysis. A further sensitivity analysis will be carried out using the data set with all available cases (without any imputation of missing data). The secondary outcomes as well as a potential moderating role of individual and family-level variables and adherence to the intervention and engagement in home practice will be examined in an exploratory manner with appropriate methods. The other model parameters will be set as in the primary outcome analysis. The safety endpoints will be determined using frequency tables and, if possible, using mixed logistic regressions to compare the event frequencies. Interim analyses are not planned. A detailed statistical analyses plan will be prepared and finalized before the code is broken. Statistical analyses will be carried out with SPSS Version 23 or newer (IBM Corp., Armonk, NY, USA).

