### Methods against bias

We take the following action to minimize potentials for biased results. Assessments will be conducted by trained interviewers unaware of the study condition, at home and individually in separate rooms for participating family members to ensure privacy and confidentiality and to reduce drop-out. Blinding of families and intervention facilitators is not possible. To maintain program retention, during the family sessions we offer child care for families who have younger siblings they cannot leave at home alone [69]. Moreover, participating families will be financially rewarded for complete program retention and for each completed follow-up data collection. To avoid crossover in the intervention groups, we aim for implementation of parallel group training with regard to both intervention conditions.

Data management will be performed locally following the guidelines of Good Clinical Practice (GCP) and will be monitored (including source data verification), collected, and preprocessed by the Clinical Trial Center North, thus an external clinical research organization (CRO).

A Data and Safety Monitoring Board (DSMB) will be implemented once the recruitment has started with regular meetings (preferably by telephone conferences), with an open and closed part with and without the coordinating investigator. The DSMB will monitor study and recruitment progress, protocol deviations, loss-to-follow-up data, serious adverse events (SAE) and adverse events (AE), and all problems of the study and decide independently from the coordinating investigator whether the study can be continued or a recommendation is given to change the design or stop the trial. The members of the DSMB will be experienced scientists who are not otherwise involved in the study, independent of the investigators and the trial sponsor, and will have no conflict of interests.

Recruitment centers and all researchers conducting the consenting process and baseline assessments will be repetitively trained to conceal any information which could lead the participants to associate an intervention timing with an intervention arm in order to improve allocation concealment.

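### Families who can attend only one slot get their arm from their timetable, not from the draw, and the plan keeps them in the confirmatory contrast without saying in which arm they count

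*Protocol article*

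**What the plan says.** All places are in the protocol article, Methods/design.

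- **Randomization procedure and blinding.** Families are allocated 1:1, stratified by recruitment center and intervention cycle. Before assignment, an independent researcher receives a coded identifier for each family, "including information on absolute time restrictions for participation". The override follows: "In the case that a defined time restriction of one family means incompatibility with the randomly allocated intervention timing", then "the family will be allocated to the other intervention arm by the independent researcher". The stated reason is to secure participation. For moved families, "the index identification code will be separately reported to the study team after the allocation process is finalized to allow for methodological scrutinization".
- **Analysis plan.** The intention-to-treat population is defined as "including data from all participants who provide baseline data and are subsequently randomized to one of the two trial conditions". The group contrast at the 18-month follow-up is the confirmatory test. Two sensitivity analyses are named: "An additional analysis will be conducted on a per-protocol data set as sensitivity analysis", and one on all available cases without imputation. Neither is defined by time restriction or reallocation, and the arm in which a moved family is analysed is not given.
- **Methods against bias.** Staff are trained to "conceal any information which could lead the participants to associate an intervention timing with an intervention arm".

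**The concern.** For a family that can attend only one of the two slots, the draw has no influence on the program it receives. If it draws the compatible arm it stays; if it draws the other arm it is moved. Its probability of reaching the compatible arm is 1 instead of 0.5.

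The reported codes show only the families that were moved. Single-slot families that happened to draw the compatible arm look like ordinary randomised families. Removing the reported codes alone would leave this second half sitting in one arm.

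The consequence depends on the unstated arm of analysis. Counted where they were moved, the arms can differ by whatever goes with limited availability, such as carers' working patterns, and that may relate to adolescent drinking. Counted as first drawn, the comparison stays randomised, but some families received the other arm's program and the contrast shrinks.

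**Working it through.** **Inputs from the article (Sample size).** d = 0.40, two-sided α = 5%, power 80%, baseline to follow-up correlation r = 0.30, 91 per arm, 15% loss, 216 families in total.

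**Assumed, because the article does not give them.** The share q of single-slot families (5%, 10%, 20%); how their restrictions split between the arms' slots; the prognostic difference D between single-slot and other families (0.2 or 0.5 SD).

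**1. The plan's own figure.** Residual SD = √(1 − 0.30²) = 0.954. With a noncentral t distribution, 91 per arm gives 80.3% power and 90 gives 79.9%, so 91 is reproduced. Inflation per arm: 91/0.85 = 107.06, rounded up to 108, and 2 × 108 = 216. No stated figure is wrong. The calculations below use the same simple ANCOVA setting with 91 per arm and ignore clustering by intervention group.

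**2. How many families are affected.** A single-slot family draws the incompatible arm with probability 0.5. If a share f of families is moved, the share allocated by timetable is on average q = 2f. For example, 5% moved (about 11 of 216) means about 10% allocated by timetable.

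**3. Counted as first drawn.** On average q/2 of all families receive the program they did not draw, so the effect becomes 0.40 × (1 − q). This holds whichever way the restrictions split between arms.

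| q | effect | power, 91 per arm |
|---|---|---|
| 5% | 0.38 | 76% |
| 10% | 0.36 | 72% |
| 20% | 0.32 | 61% |

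**4. Counted in the arm they were moved to.** If every single-slot family fits the same arm, their share in that arm is s = q / [q + (1 − q)/2], and it is zero in the other. The bias is s × D. At q = 10%, s = 0.10 / 0.55 = 18.2%.

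| q | s | bias, D = 0.2 | type I error | bias, D = 0.5 | type I error |
|---|---|---|---|---|---|
| 5% | 9.5% | 0.02 SD | 5.2% | 0.05 SD | 6.3% |
| 10% | 18.2% | 0.04 SD | 5.8% | 0.09 SD | 9.8% |
| 20% | 33.3% | 0.07 SD | 7.6% | 0.17 SD | 21.6% |

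This table is the one-sided extreme. If the restrictions split 75/25 between arms at q = 10%, the bias is 0.02 SD (D = 0.2) or 0.05 SD (D = 0.5), with type I error 5.2% or 6.2%. If they split evenly, the expected bias is about 0.

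**5. Only families free for both slots.** Their allocation is the random draw, so the comparison is randomised and undiluted. The number per arm becomes 91 × (1 − q) = 86, 82 and 73, and power is 78%, 76% and 71% at q = 5%, 10% and 20%.

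**The case against.** The rule is disclosed and justified, and safeguards surround it. Only absolute restrictions count, and they are passed on before assignment. The researcher who moves families is independent and sees only codes. Staff are trained to hide which slot belongs to which program. The article also aims to run the two conditions in parallel; if that means at the same hours, clashes would be rare. At six to eight families per arm and cycle, 216 families need about 14 to 18 cycles (216/16 = 13.5; 216/12 = 18), so restrictions need not keep favouring one arm. A flow chart of the procedure and a detailed analysis plan are announced but not shown, and either could settle the arm of analysis.

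Much of this stands as a limit on size. It makes deliberate selection unlikely and a bias near zero quite possible. It does not restore random assignment for single-slot families, because the override is fixed once slot and restriction are known. A later analysis plan can choose the analysis set, but it cannot make that allocation random. Nothing shown ensures balance, for example a random match of program to slot.

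Three stronger readings are tempting and not supported:

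- **That the randomised superiority test is lost either way.** Analysis by first-drawn arm is a valid randomised test, only less powerful.
- **That the result is biased by a known amount.** The 0.09 SD figure needs an assumed 10% share, all restrictions favouring one arm across the trial, and a 0.5 SD difference. The article gives none of these.
- **That families will choose their arm by declaring a restriction.** The article describes measures against this and gives no sign that it happens.

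**Conclusion.** The point holds in conditional form. The override makes the arm of every single-slot family a matter of timetable, and the intention-to-treat definition retains these families without saying where they are counted. Because the article treats the move as part of the allocation process, the moved-to arm is the natural reading, though it is not stated. On that reading part of the confirmatory contrast is not randomised, with a bias whose size and direction cannot be derived: at an assumed 10% single-slot families, from about 0 to 0.09 SD, the latter a little under a quarter of the planned d = 0.40 (0.09/0.40 = 23%). On the alternative reading the test is sound and the loss is power alone. At each assumed share, restricting to families free for both slots loses less power than the dilution does (78/76/71% against 76/72/61%) and also removes the timetable confounding.

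**What to change.** **Future cycles.**
- Use the restrictions already supplied before assignment to decide who enters the draw, and randomise only families able to attend both slots.
- Single-slot families may join the group they can reach, which keeps the aim of participation, but they are not counted as randomised.
- Where facilitator availability allows (SFP-Mind needs facilitators with mindfulness training), have the independent statistician draw at random which program runs in which slot, after restrictions are locked.

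**Cycles already allocated** (recruitment began in December 2019).
- Do not analyse by the moved-to arm.
- Choose one of two primary approaches before the code is broken, and report the other as sensitivity analysis: (a) all families recorded before allocation as free for both slots, excluding every single-slot family in both arms and not only those moved; or (b) all families in the arm originally drawn, which the reported codes allow to be reconstructed.
- Report the numbers of single-slot and moved families by arm.

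**Cost.** An amendment to the protocol and the randomisation procedure. No new data are needed, provided the pre-allocation restriction records are kept. Option (a) costs about 4 power points at 10% single-slot families (80% to 76%). If these families are not replaced by further recruitment, the power statement has to be restated.

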### Interventions

#### SFP 10–14 (control)

Families in the control group will participate in the standard SFP 10–14, which is a highly structured and evidence-based prevention program for families at the universal prevention level [27]. ›*Familien stärken*‹ is the certified German version, which relies on a video/DVD-based approach to learning the same as the original US program. In the narrated videos, participants see typical family interactions in diverse families and settings. To accommodate a contemporary urban setting and to increase authenticity and credibility, in extensive pilot work the original US-version video material was presented and discussed in focus groups of target families and translated as well as culturally adapted [68]. The program features seven weekly sessions of approximately 3 h. Per session, three group facilitators simultaneously work with 8–12 families, with parallel sessions for parents and adolescents during the first hour and sessions for the entire families during the second hour. All sessions include DVD presentations, role-plays, group discussion, input, social bonding, and skill-building activities. At the end of the program, a family meal is also provided to strengthen support and sharing between families. For more information on program content, see Bröning et al. [69].

#### SFP-Mind (experimental intervention)

The development of the experimental SFP-Mind intervention (›*Familien achtsam stärken*‹ [Strengthening Families with Mindfulness]) is part of the ongoing study. Implementation procedures and participant satisfaction were qualitatively assessed in a pilot intervention based on a small sample of target families (*N* = 5). SFP-Mind will integrate intrapersonal and interpersonal mindfulness practice into the evidence-based SFP 10–14 while maintaining the validated structure of the original program.

We focus on teaching mindfulness to adolescents to target the neurobehavioral, self-regulatory mechanisms implicated in developmental pathways of addictive behavior (such as reward and response inhibition, impulsivity, and emotion processing) and to strengthen developmental competencies. But the novel program also provides mindfulness modules for parents to support their own and adolescent mindfulness activities outside the regular weekly group sessions, which are derived from programs of mindful parenting [62–65].

This approach targets the family as a system and reflects a developmental perspective in which parents are considered influential agents for adolescent development. We assume that mindfulness holds particular promise because it can help manage instability of intrapersonal and interpersonal affective states (e.g., stress, anger, negative mood), which commonly exists at the family level in this developmental period, and often predicts substance use [26, 70]. The newly added mindfulness program modules (e.g., focused attention, deep breathing, cultivating a kind attitude toward self and others, setting positive intentions) draw on youth-specific adaptations of mindfulness-based interventions (such as the 8-week curriculum of mindfulness-based cognitive therapy, MBCT), but will be relatively brief compared to other formal mindfulness interventions, and will be designed to reflect age-related developmental needs and characteristics of youth 10–14 years old (e.g., with regard to attention span, cognitive capacities, language, physicality, relevant content, time involved in the intervention, and home practice in a situation with competing time demands). The selection of age-appropriate mindfulness modules for our targeted population builds on the current knowledge base of mindfulness training in non-clinical youth populations, which mainly derives from established school-based approaches [71], such as the “Learning to Breathe” manual [72, 73] and other programs [74, 75].

The new mindfulness components will be integrated into the parallel adolescent-directed, parent-directed, and family-directed sessions in the seven consecutive sessions with emphasis on one thematic key aspect of mindfulness per week. The seven thematic key aspects will be Breath, Attention/Awareness, Body/Stress, Feelings/Emotions, Thoughts, Compassion/Happiness, and Mindfulness in Everyday Living. Consideration of youth-specific needs for experiential, interactive, and skill-oriented learning are the guiding principles in the development and integration of the mindfulness modules.

One goal is to stimulate mindfulness practice outside the weekly program sessions. Participants will thus be strongly encouraged to practice meditation and MT on a daily basis and to protocol their practice on diary cards. Parents will be instructed to support adolescent home practice. Moreover, home practice MT-related content, such as guided meditations, will be provided in written form as well as in audio files and a computer/smartphone app. This material will be specifically developed for study purposes and serves as a practical and user-friendly method to foster home practice of program content. Importantly, the app is therefore not designed to collect data (however, frequency of use of app content will be analyzed). Use of the app is voluntary, as not every child may have access to a tablet or smartphone, and will be fully compatible with German regulations of data security. Existing integrations of (parent-directed) mindfulness training into the SFP 10–14 [64, 65] indicate that facilitating mindfulness practice via didactic presentations about principles of mindfulness, modeling of mindfulness practices, and group interactive discussions are feasible formats to accommodate a family-based substance use prevention setting. Additional file 1 provides a schematic overview of the experimental and control interventions.

